**Methods/Design:**

A cluster randomised school drug education trial will be conducted with 1746 junior high school students in 21 Victorian secondary schools over a period of three years. Both the schools and students have actively consented to participate in the study. The education program comprises ten lessons in year eight (13-14 year olds) and eight in year nine (14-15 year olds) that address issues around the use of alcohol, tobacco, cannabis and other illicit drugs. Control students will receive the drug education normally provided in their schools. Students will be tested at baseline, at the end of each intervention year and also at the end of year ten. A self completion questionnaire will be used to collect information on knowledge, patterns and context of use, attitudes and harms experienced in relation to alcohol, tobacco, cannabis and other illicit drug use. Multi-level modelling will be the method of analysis because it can best accommodate hierarchically structured data. All analyses will be conducted on an Intent-to-Treat basis. In addition, focus groups will be conducted with teachers and students in five of the 14 intervention schools, subsequent to delivery of the year eight and nine programs. This will provide qualitative data about the effectiveness of the lessons and the relevance of the materials.

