## Methods/design

### Study design

Twenty one Victorian government high schools have been recruited to the study. The schools were then allocated to four strata: six schools to metro location, high SES; three schools to rural location, high SES; six schools to metro location, low SES; six schools to rural location, low SES. This approximated the proportion of Victorian secondary schools in each category. Within each strata the schools were then randomly allocated to intervention or control conditions on a two to one proportion to allow more precise statements about the effects of the intervention [31]. Random allocation and allocation concealment were achieved by one member of the research team writing the names of each school on identical paper chits which were then folded to conceal the name. The same researcher also created seven chits with the word control and 14 with the word intervention. These were similarly folded to conceal the words. The chits with the school name and those designating allocation were placed in separate containers. A different member of the team then simultaneously drew out a chit with the name of a school and a chit designating either control or intervention allocation.

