### Sample

The participating students attended the 21 Victorian government secondary schools that had agreed to participate in this project. Four schools are located in metropolitan Melbourne; ten are located in metropolitan fringe and major regional areas; and seven are in regional and rural areas. The student populations of six schools are in the medium high/high range in term of socioeconomic status, as measured by the Department of Education and Early Childhood Development's (DEECD) Student Family Occupation (SFO) index. The student populations of ten schools are in the medium range. The student populations of five schools are in the low range. Written active consent was sought from the 2700 year eight students in the 21 participating schools and their parents. Of this total population 1746 or 64.7% agreed to participate in the research. Intervention students numbered 1230. Control students numbered 516.

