### Statistical analysis

Multi-level modelling can best accommodate hierarchically structured data and will be used in this analysis, adjusting for any baseline differences between the intervention and control groups [42,43]. The hierarchy in this longitudinal multi-level dataset comprises level 1 units (occasions of repeated measurement), nested within the level 2 units (the individual student), nested within the level 3 units (the school). Stata version 10.0 will be used for model fitting, with a three-level mixed regression model fitted to the data to account for the repeated observations [44]. If necessary, the knowledge, consumption and harm scales will be log-transformed to satisfy the assumption of normality. If normality cannot be achieved by log-transformation, non-parametric procedures will be used for analysis. All analyses will be conducted on an Intent-to-Treat basis. Complete-case analysis (CCA) will be complemented with multiple imputation analysis (MIA) to account for missing data.

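### The three-level model is described with no term for school-specific change; with intercepts only, a group-by-occasion test would be too liberal if schools differ in trend

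*Protocol article*

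**What the plan says.** The Statistical analysis section of the Protocol article sets out a hierarchy that "comprises level 1 units (occasions of repeated measurement), nested within the level 2 units (the individual student"), themselves "nested within the level 3 units (the school"). It names Stata 10.0, "with a three-level mixed regression model fitted to the data to account for the repeated observations", and says the analysis will adjust for baseline differences between the groups. School appears only as the top nesting level. The section does not list the random effects, and it names neither a reference distribution nor a degrees-of-freedom method.

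Three other places bear on the point:

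- Under Sample size calculation, the primary outcome is described as a change in alcohol consumption patterns and associated harm.
- Under Study design, schools were allocated 2:1 within four strata, using "seven chits with the word control and 14 with the word intervention". The same section says each control school runs its own usual drug education, and that in year ten every school returns to its own usual curriculum.
- The abstract gives four measurement occasions: "Students will be tested at baseline, at the end of each intervention year and also at the end of year ten".

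**The concern.** When the outcome is a change and there are four occasions, the natural test of the intervention in this model is a group-by-occasion contrast. A school random intercept is constant over time, so it drops out of any baseline-to-post difference. If it is the only school-level term, the contrast is tested against the within-student residual, as though all students changed independently of their school. The randomised unit is the school, so the error for this contrast should include how much schools differ in their change.

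The article itself gives reasons to expect such differences. The comparator varies from one control school to the next. The Background reports that fidelity tends to break down when lessons are interactive. The schools also span metropolitan, regional and rural areas and several socioeconomic bands.

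At stake is a main comparison with standard errors that are too small. Because the model is called multilevel, readers may take clustering to be fully handled.

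**Working it through.** **The plan's own figure.** The sample size reproduces if .15 is read as Cohen's f for a between-groups effect in a repeated-measures ANOVA with 4 occasions and a within-student correlation of 0.5 (the test family and the correlation are assumptions). Then λ = 0.15² × 364 × 4 / (1 + 3 × 0.5) = 13.1, which gives power 0.951 at N = 364. Multiplying, 364 × 1.48 = 538.7, or 539. This is a group difference averaged over occasions. The group-by-occasion version with the same inputs gives 98. The sample size section therefore supplies no figure for school-by-occasion variance.

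**Inputs.**

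- Schools: 14 and 7 (Study design). Between-school degrees of freedom are 21 − 2 = 19, or 19 − 3 = 16 after fitting four strata.
- Students: "Intervention students numbered 1230. Control students numbered 516" (Sample). The mean is 1746/21 = 83.1 per school (87.9 intervention, 73.7 control).
- Students remaining per school after 15% yearly loss for three years (the rate is quoted under Sample size calculation from the earlier school alcohol project): 83.1 × 0.85³ = 51.1.
- Assumed: within-student correlation ρ = 0.5, and school-by-occasion variance τ as a share of total variance, over a range. The article gives neither.

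**Variance of the contrast.** Set total variance to 1, with ρ held by the school and student intercepts. For a baseline-to-post difference both intercepts cancel. With m students in a school, the true variance of the school's mean change is 2τ + 2(1 − ρ − τ)/m. A model without the school-by-occasion term uses 2(1 − ρ)/m. The ratio is

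R = 1 + τ(m − 1)/(1 − ρ),

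and the actual type I error of a nominal two-sided 5% z test is 2[1 − Φ(1.96/√R)].

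Worked example, m = 51, τ = 0.005, ρ = 0.5: R = 1 + 0.005 × 50/0.5 = 1.5; 1.96/√1.5 = 1.60; type I error = 0.110.

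**Results, no school-by-occasion term.** Simulated values use 20,000 trials of 14 v 7 schools, with 54 and 45 students per school after attrition or 88 and 74 as enrolled.

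| τ | m = 51: R | formula | simulated | m = 83: R | formula | simulated |
|---|---|---|---|---|---|---|
| 0 | 1.00 | 5.0% | 4.9% | 1.00 | 5.0% | 4.9% |
| 0.0025 | 1.25 | 8.0% | 7.6% | 1.41 | 9.9% | 9.3% |
| 0.005 | 1.50 | 11.0% | 10.7% | 1.82 | 14.6% | 14.2% |
| 0.01 | 2.00 | 16.6% | 15.8% | 2.64 | 22.8% | 22.2% |

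A separate simulation with all four occasions, 51 students per school and a school intraclass correlation of 0.01 (4,000 runs) gave 4.5%, 8.2%, 10.9% and 15.7% for the same four values of τ. A higher within-student correlation makes matters worse: at ρ = 0.7, m = 83 and τ = 0.005, R = 2.37 and the formula gives 20.3%.

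**Few schools alone.** With the right variance but a normal cut-off, P(|t| > 1.96) is 0.065 on 19 df and 0.068 on 16 df.

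**Check of the remedy.** Testing school-level changes against t on 19 df gave 5.1% to 5.7% over τ from 0 to 0.02, at both school sizes.

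**The case against.** The strongest reply is that the article names levels, not random effects. A three-level model can carry a school-level time slope, nothing in Statistical analysis rules one out, and a journal article commonly leaves such detail to a fuller document. That stands as far as it goes: a reader might infer that the plan omits school-specific change, or that its test is bound to be too liberal, and the text supports neither. What remains is that the model is described in some detail, school appears only as a nesting level, and the ordinary intercepts-only fit of that description gives the wrong error term for differential change.

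Second, adjustment for baseline differences could mean post-test scores with baseline as a covariate and a main effect of arm. Under that reading the school intercept does not cancel and supplies the error for the averaged effect. The reading is possible, but the article does not settle it, and framing the primary outcome as a change points towards group-by-occasion at least as readily.

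Third, the inflation figures rest on an assumed variance range, and at zero variance the test holds its level. That is correct, and the figures should be quoted only with those assumptions.

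Fourth, a reader might blame the seven control schools equally. The calculation does not bear this out. Few schools add about 1.5 percentage points, and only with normal cut-offs, which the article does not specify.

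**Conclusion.** The point holds conditionally. Three things must be true together: only school and student intercepts are fitted, the effect is tested as group-by-occasion, and schools differ in trend. Type I error is then about 8%, 11% and 16% for school-by-occasion shares of 0.25%, 0.5% and 1%, at 51 students per school and a within-student correlation of 0.5. At the enrolled 83 per school it is about 9%, 14% and 22%. The article gives no value for the variance share, but with comparators and delivery that differ by school, exactly zero is hard to defend as a working assumption. The small number of schools is a secondary issue.

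This is not a plan that ignores clustering, since school is named as a level. The weakness is that the described structure, taken at face value, does not protect the contrast that matters most. It should be corrected before the analysis.

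**What to change.** Choose one of two specifications and state it:

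- Keep the three-level model and add a school-by-occasion random effect or a random school slope, so that the group-by-occasion contrast draws its error from variation between schools.
- Model post-test scores adjusted for baseline, with a school random intercept, either at each post-test or as an effect averaged over them.

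In either case, refer the intervention term to t on school-level degrees of freedom (19, or 16 with strata fitted) or to the permutation distribution of the stratified allocation. If the 2:1 ratio was kept within the strata of 6, 3, 6 and 6 schools, there are 15 × 3 × 15 × 15 = 10,125 possible allocations, which is ample.

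The cost is one extra variance component and slightly wider intervals. The t reference on 19 df widens them by about 7% (2.093/1.960). Any further widening arises only to the extent that schools really do differ in trend.

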### Sample size calculation

The ability to detect small changes in substance use, knowledge, attitudes and harms experienced is central to this study. The primary outcome is a change in alcohol consumption patterns and associated harm, and accordingly sample size estimations are based on detecting a small effect size of .15 in relation to these measures. This effect size was chosen on the basis of previous school drug education studies [9,32].

The target sample size has been estimated using G*Power v.3.1.3 software where α = 0.05 and 1-β error probability = 0.95 [33]. Assuming simple random sampling, a total sample size of 364 is required at the end of the study. However, there is a design effect due to the loss of effectiveness created by cluster sampling. The design effect for the SHAHRP study, which took into consideration the effect of clustering by school and a 15% annual rate of student attrition, was calculated to be 1.48. Using this correction, a total sample size of at least 539 is required to test the effectiveness of the intervention.

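### The fallback to unnamed non-parametric procedures, likely to be reached for the zero-prone primary scores, does not guarantee that school clustering, repeated measures and baseline adjustment are kept

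*Protocol article*

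**What the plan says.** The Statistical analysis section of the protocol article gives the main method and its reason: "Multi-level modelling can best accommodate hierarchically structured data and will be used in this analysis, adjusting for any baseline differences". The levels are occasion, student and school, "with a three-level mixed regression model fitted to the data to account for the repeated observations".

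Two sentences then deal with non-normal scores. The first is "If necessary, the knowledge, consumption and harm scales will be log-transformed to satisfy the assumption of normality". The second is "If normality cannot be achieved by log-transformation, non-parametric procedures will be used for analysis". The procedures are not named, and no criterion for normality is given.

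The Sample size calculation section shows which outcomes this affects: "The primary outcome is a change in alcohol consumption patterns and associated harm". The same section inflates the sample by a design effect that allows for clustering by school. The Study design section states that whole schools were randomised, 14 to intervention and 7 to control.

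**The concern.** The rule treats non-normality as a reason to leave the multilevel model. Distribution and hierarchy are separate matters. A skewed or zero-heavy score calls for a different outcome distribution or for robust inference, while the nesting of occasions in students and of students in schools stays as it was.

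The rule bears on the primary outcome. Most students are 13 at baseline, and the hypothesis speaks of taking up use, so non-users are expected. The harm scales have only 5 to 10 items per drug type. If non-users are scored zero, log(0) is undefined, and adding a constant before taking logs only moves the spike to another value. The condition for the fallback would then be met.

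The familiar rank tests treat students as independent, take one occasion at a time and do not adjust for baseline. In a trial that randomised 21 schools, such a test gives p-values that are too small.

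**Working it through.** **The plan's own figures.** The article requires 364 students before clustering and 539 after. The second follows from the first: 364 × 1.48 = 538.7, rounded up to 539. The 364 is reproduced by a repeated-measures ANOVA between-group test with f = 0.15, two groups, four occasions, within-student correlation 0.5, alpha 0.05 and power 0.95. The f metric and the correlation are assumptions, as the article states neither. This point does not depend on them. What matters is that the plan counts clustering as a material loss when it sizes the trial.

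**Would the fallback be reached?** Scores with 10%, 20%, 50% and 80% zeros (an assumed range) were simulated for about 1,070 students, which is 1746 × 0.85³. A Shapiro test on log(y + 1) rejected normality in every one of the 100 runs checked per setting. Both the Shapiro test and its use on raw scores are assumptions.

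**Size of the error if schools are ignored.** Inputs:
- 1,746 students in 21 schools (Sample section): 1746 / 21 = 83.1 per school at baseline.
- 85% retained per year, from the 15% annual attrition that the article cites for the earlier study. Over an assumed three years: 83.1 × 0.85³ = 51.1 per school.
- ICC: not given in the article; 0.005 to 0.05 assumed.

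Formulas: DE = 1 + (m − 1) × ICC, and real two-sided alpha = 2 × (1 − Φ(1.96 / √DE)).

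At the article's 1.48: 1.96 / √1.48 = 1.611, so alpha = 0.107.

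| ICC (assumed) | DE, m = 51.1 | alpha | DE, m = 83.1 | alpha |
|---|---|---|---|---|
| 0.005 | 1.25 | 0.080 | 1.41 | 0.099 |
| 0.01 | 1.50 | 0.110 | 1.82 | 0.146 |
| 0.02 | 2.00 | 0.166 | 2.64 | 0.228 |
| 0.05 | 3.50 | 0.295 | 5.11 | 0.386 |

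**Check by simulation.** Zero-inflated scores were generated with no intervention effect in 14 + 7 schools, 1,000 runs per setting, with the ICC set on the latent scale. The rank-sum test that ignores schools rejected in these proportions, across the four zero shares:
- ICC 0: 0.051 to 0.055
- ICC 0.005: 0.052 to 0.087
- ICC 0.01: 0.082 to 0.102
- ICC 0.02: 0.115 to 0.169
- ICC 0.05: 0.206 to 0.286

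A t-test on school mean ranks, which keeps the school as the unit, stayed between 0.039 and 0.065. The inflation therefore comes from ignoring schools and not from the use of ranks.

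**The case against.** The strongest reply is that the article never says clustering is abandoned. It names no procedure, and non-parametric methods that respect clusters exist. A permutation test of school allocation, recommended below, is one of them. This stands. A reader might infer that the fallback drops clustering, repeated measures and adjustment, but the text supports only that it gives no assurance of keeping them.

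A second reply is that the trigger is not documented. The article gives no share of zeros, no score distribution and no rule for scoring non-users. An analysis among users only is not excluded. In a mixed model the normality assumption concerns residuals and random effects, not raw scores. This also stands in part: a reader might call the fallback almost certain, but the documents support only that it is likely.

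Third, the 1.48 is not a pure variance inflation factor for this trial. It was calculated for an earlier study and includes attrition. Hence 10.7% is an approximation and should not be read as the error rate at this trial's own design effect.

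Fourth, a main method with a conditional fallback is not, strictly, a contradiction. That is fair. The conflict is with the reason given for the main method, because the nesting does not go away when the scores are skewed.

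Finally, one could say that the choice of procedure belongs in an analysis plan not shown here. That would hold if the article were silent. Instead it states a decision rule that takes the primary scores out of the model it has just justified, and nothing elsewhere in the article limits that rule.

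**Conclusion.** The concern holds in a conditional form. The article fixes a rule under which the primary consumption and harm scores may leave the three-level model for unnamed procedures, with no statement that schools, repeated occasions and baseline values remain accounted for. That the rule will be reached is likely but not certain; it rests on non-users scoring zero in appreciable numbers.

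If ordinary rank tests were then used, the nominal 5% error would be roughly doubled at a design effect of 1.48. It would lie between about 8% and 30% for ICCs of 0.005 to 0.05 at about 51 students per school. These ICCs and the three-year retention are assumptions. If a procedure that respects schools were used, the error would stay near 5%. The text leaves both outcomes open for the main result of the trial, so the rule should be settled before outcome data are analysed.

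**What to change.** For consumption and harm, replace the log-transformation and non-parametric rule with a mixed model chosen in advance for scores with many zeros: negative binomial, two-part or ordinal. Keep the school and student random effects and the baseline adjustment already planned.

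Limit any distribution-free analysis, for the knowledge scale as well, to one that respects school randomisation. A suitable choice is a permutation test of school allocation within strata on baseline-adjusted school summaries. With strata of 6, 3, 6 and 6 schools and two-to-one allocation held exactly in each, the number of possible allocations is C(6,2) × C(3,1) × C(6,2) × C(6,2) = 15 × 3 × 15 × 15 = 10,125, which is ample for an exact test.

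The cost is a change of wording and modest programming, including a check that the chosen software fits the model. No data collection changes. The downside is that effects from these models are expressed as ratios and not in scale units, which needs some care in reporting.

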## Discussion

The benefits of undertaking this harm reduction focused drug education demonstration program derive both from the knowledge gained by trialling an optimum combination of evidence derived approaches with a large, representative student sample, and the resultant product. The program targets alcohol, tobacco and illicit drug use; draws on research that consistently identifies a core set of effective practice elements and is rigorously evaluated over an extended period. The program also does not simply rely on the traditional measures of effectiveness, namely abstinence or reduced use. Harms associated with use are also measured as valid indicators of program effect. This will provide a broader understanding of what benefits can be achieved by school drug education. By the end of the study a well documented, comprehensive drug education package will have been produced. It will be of a size able to be accommodated within a secondary school's health curriculum and the evaluation findings will provide evidence as to its potency. This makes available to schools a readily useable drug education program with well understood prevention characteristics.
